### Subjects/population

#### Recruitment of chiropractors

A sampling frame of 8200 chiropractic practices within 10 provinces in Canada will be obtained from the Canadian Chiropractic Association (CCA). From this, a random sample of 200 chiropractors will be selected and approached for participation in this study [33, 34]. A sample of 200 chiropractors has been chosen as we expect that 20 % of eligible chiropractors will agree to participate (i.e. recruitment rate), and from these, 80 % will complete the study at 3 months (retention rate). Chiropractors who agree to participate and meet the eligibility criteria will be randomized. If we are unable to recruit the required sample of 30 from the first wave of 200 chiropractors, an additional 200 chiropractors will be randomly sampled.

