### Measures

The key feasibility outcomes of interest include (1) study recruitment/participation, (2) adherence to the intervention, (3) study retention, and (4) KT intervention effectiveness potential. Table 1 provides the different criteria for defining the outcomes derived from items (1) to (4) above. Table 2 further summarizes the feasibility outcomes, sources of measurement, and timing of administration.

**Table 1 Tab1:** Criteria to assess feasibility

Construct	Parameter
	Eligibility proportion
Chiropractors	
Recruitment	Trial acceptance rate: >20 % agree to participate within 4 weeks
	Target population = 40 (assuming an 80 % retention rate)
Adherence to protocol	>90 % of participants will complete all 3 webinars, associated quizzes, 2 clinical vignettes, and a self-management learning module
Retention	80 % of participants will complete 3 months of patient follow-up
Patients	
Recruitment	Trial acceptance rate: 5 patients within 6 weeks of recruitment notice
	Target population = 150
Adherence to protocol	95 % will attend regular treatment sessions twice/week
	>80 % will comply with prescribed home exercise and physical activity
Retention	>80 % will complete patient encounter forms (VAS, NDI, and PSQ-18) and follow-up at 3 months

**Table 2 Tab2:** Outcome measures

Outcome	Source	Description of measures	Data collection time points	
Feasibility				
Recruitment	Chiropractors and patients	Measured as a proportion of chiropractors and patients potentially eligible for participating	Initial stage	
		Eligibility rate = number of eligible chiropractors and patients divided by the number of invited chiropractors or patients		
		Participation rate = number of chiropractors and patients agreeing to participate divided by number of eligible chiropractors and patients		
Adherence to protocol	Chiropractors	For those randomized to intervention arm, measured through the rates of attendance of all 3 webinars, associated quizzes, completion of 2 clinical vignettes, and the self-management learning module	Within 6 weeks of assignment	
	Patients	Rate of adherence to follow-up visits, prescribed home exercise, and physical activity	Baseline	3 months
Adherence perception (knowledge and self-efficacy)	Chiropractors and patients	Completion of questionnaires	Baseline	3 months

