Retention	Chiropractors and patients	Retention rate = number of chiropractors or patients who completed follow-up of all outcome measures at 3 months divided by number of chiropractors or patients who were randomized	Baseline	3 months
	Chiropractors	Rate of completion of patient encounter forms and questionnaires including levels of knowledge and self-efficacy and the BAP	Baseline	3 months
	Patients	Rate of completion of patient encounter forms and questionnaires including the BAP, visual analogue scale (VAS), Neck Disability Index (NDI), and satisfaction with care	Baseline	3 months

Differential retention and adherence rates across the randomized groups will also be measured

Expected adherence to multimodal care by chiropractors will be measured at the end of the study using a short self-administered questionnaire that will include items about knowledge (e.g. “I am following the recommendations regarding the use of clinical practice guidelines and multimodal approach for neck pain”) and self-efficacy (e.g. (i) “I am confident that I will not encounter difficulties in delivering multimodal care” and (ii) “If I encounter difficulties, I am confident that I can still offer multimodal care”) [29, 35, 36]. End-of-study questionnaires will also include the Brief Action Planning (BAP) skill survey and clinician experience in using the BAP tool in practice (Additional file 1).

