### Procedures

The CCA and provincial chiropractic associations will be asked to promote the study via their newsletters and by emails to chiropractors informing their members of the study purpose and encouraging them to participate in this study. An invitation letter with the McGill University letterhead, with a consent form, a demographic questionnaire, and a prepaid stamped and self-addressed envelope, will be sent to the sample of 200 chiropractors. Chiropractors expressing an interest in participating will receive a follow-up letter written in a standardized format, giving information about the study project. A follow-up invitation and a reminder to participate will be sent if initially an insufficient number of clinicians are enrolled. As an incentive to participate, chiropractors who complete all aspects of the study will be entered into a draw to win one of four $250 gift cards as a token of appreciation. In addition, most provincial chiropractic regulatory boards have pre-approved the KT intervention for 4 h of Continuing Education (CE). Certificates of completion are produced once the KT intervention is completed by chiropractors and all quizzes have been successfully answered. Obtaining a credit for the course may contribute to participant confidence regarding the experimental KT intervention and may improve study adherence.

In order to determine the eligibility of the participating chiropractors, a demographic questionnaire will be sent with the invitation package to inquire about their age, sex, years in practice, practice location (rural versus urban), chiropractic school attended, type of practice (solo versus multidisciplinary clinic), main chiropractic techniques/approaches used (e.g. diversified, Gonstead, BCP), and professional membership status.

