### Statistical analysis

The main analysis will focus on descriptive statistics relating to feasibility to estimate likely recruitment and retention rates, adherence to the intervention, and provide key parameters, e.g. effect size needed to decide on a primary outcome and to estimate the sample size for a full-scale study. Also, we will estimate the potential efficacy of the intervention on adherence to the recommended multimodal approach for NSNP and on patient outcomes of pain and disability. Instead of calculating an average response on each measure for each group and comparing means between groups, this study will identify the proportion of people in each group making a treatment response, which will then be compared between groups. Each person will be classified as having made a response, a deterioration, or no change on each measure based on a change equal to or greater than the MCID published or recommended for that measure. Table 4 provides the summary of this analysis.

**Table 4 Tab4:** Statistical analysis

Construct	Measure	Measurement scale
Feasibility of recruitment, retention, and data completion (both chiropractors and patients)	Recruitment and retention rates, missing data	Descriptive statistics: mean and SD for continuous variables and proportions for categorical variables
Chiropractor process outcomes		
Adherence rate	Single indicators	Continuous data (number of DCs adhering to the intervention per number of eligible participants)
	Composite	Count of indicators reaching “success” threshold
Behavioural	Level of knowledge and self-efficacy	5-point Likert scale (from 1 = strongly agree to 5 = strongly disagree), ordinal
Patient health outcomes		
Pain	Visual analogue scale	Self-rated level of pain on 11 points, continuous
Disability	Neck Disability Index	Scale range and subscales: 10 items in total; each item is scored from 0 to 5 (“0” = no disability and “5” = full disability) for a total of 50
Satisfaction with care	Questionnaire	Self-rated satisfaction with care measured on the short-form questionnaire rated on a 5-point Likert scale from “very satisfied” to very “dissatisfied”
Potential efficacy	Post-intervention between groups	Normal approximation to the binomial

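### Chiropractor adherence has different denominators in Tables 2 and 4, and the 20 % acceptance rate is planned per invitee but reported per eligible chiropractor

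*Protocol article*

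**What the plan says.** Recruitment, retention and adherence are the primary feasibility outcomes. Table 1 (Measures) sets the bars for chiropractors: acceptance above 20 % within four weeks, a target of 40, and more than 90 % completing the webinars, quizzes, vignettes and self-management module. It gives no denominator for acceptance and names no arm for adherence.

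**Adherence.** Table 2 (Measures) defines it this way: "For those randomized to intervention arm, measured through the rates of attendance of all 3 webinars". Table 4 (Statistical analysis) gives it as "number of DCs adhering to the intervention per number of eligible participants". Allocation is 1:1 (Design), and the webinars are released only to the intervention arm (Delivery of the intervention).

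**Acceptance.** Table 2 states: "Participation rate = number of chiropractors and patients agreeing to participate divided by number of eligible chiropractors and patients". The line above it defines an eligibility rate as eligible over invited. Under Recruitment of chiropractors, "a random sample of 200 chiropractors will be selected and approached for participation in this study", and "we expect that 20 % of eligible chiropractors will agree to participate (i.e. recruitment rate"), with a second wave of 200 if 30 cannot be recruited from the first. Under Procedures, "In order to determine the eligibility of the participating chiropractors, a demographic questionnaire will be sent with the invitation package"; the same package carries the consent form.

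**Patient retention.** Table 2 uses completers "divided by number of chiropractors or patients who were randomized", although only chiropractors are randomized.

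**The concern.** Each of these rates is read against a numerical bar in Table 1, and the results are meant to inform whether and how a full-scale trial is run. If the denominator is unsettled, the same data can pass or fail.

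For adherence, two tables in the same article give different bases. Control chiropractors cannot complete webinars that they are never given, so a base that includes them builds failure into the result.

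For acceptance, the base used to plan the mailing (everyone approached) is not the base used to report the rate (those eligible). The two coincide only if every invitee is classed as eligible. If eligibility is learned mainly from those who return the questionnaire, the reported rate describes willingness among repliers. It would not tell the planners of the main trial how many invitations they need to send.

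**Working it through.** **1. Reproduce the planned number.** Inputs from Recruitment of chiropractors: 200 approached, 20 % agreeing, 80 % retained, 30 required.

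- 200 × 0.20 = 40, which is Table 1's target.
- 40 × 0.80 = 32, which covers the 30 required.

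The figure of 40 is reproduced only when the 20 % is applied to all 200 approached, so planning treats every invitee as eligible.

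**2. Acceptance under the Table 2 definition.** Rate = agreeing / eligible. Hold agreeing at 40 and invited at 200, so agreeing / invited = 20 %. The number classed as eligible is not given; it is an assumption, varied here from 200 down to 40.

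| Classed eligible | Agreeing / eligible | Eligible / invited |
|---|---|---|
| 200 (all invitees) | 20.0 % | 100 % |
| 183 (prior registrants removed) | 21.9 % | 91.5 % |
| 100 | 40.0 % | 50 % |
| 50 | 80.0 % | 25 % |
| 40 (only those agreeing) | 100 % | 20 % |

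The 183 is 200 × (1 − 700/8200) = 182.9. It assumes that the roughly 700 chiropractors already registered for the training are spread evenly over the sampling frame of 8200.

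Low uptake can clear the bar. If only repliers are classed, and 10 agree and 10 eligible repliers decline (assumed counts), the reported rate is 10/20 = 50 % while 10/200 = 5 % of invitees agreed.

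**3. Can eligibility be settled without a reply?** The exclusion criteria describe one such check, prior registration. A checklist of reasons for not participating is also planned (Acceptability of the intervention to participants). Neither establishes a non-replier's weekly neck-pain caseload, language or internet access, all of which are inclusion criteria.

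**4. The number of invitations matters too.** Trial status reports 45 agreed and randomized but not how many were invited. One wave gives 45/200 = 22.5 %, above the bar. Two waves give 45/400 = 11.3 %, below it.

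**5. Adherence ceiling.** Suppose every intervention-arm chiropractor completes everything.

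| Randomized | Intervention arm | Both arms as base (one reading of Table 4) | Intervention arm as base (Table 2) | Completers needed for more than 90 % on Table 2's base |
|---|---|---|---|---|
| 30 | 15 | 15/30 = 50 % | 100 % | 14 of 15 (93.3 %) |
| 40 | 20 | 20/40 = 50 % | 100 % | 19 of 20 (95.0 %) |
| 45 | 22 | 22/45 = 48.9 % | 100 % | 20 of 22 (90.9 %) |
| 45 | 23 | 23/45 = 51.1 % | 100 % | 21 of 23 (91.3 %) |

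If eligible in Table 4 meant all 200 invitees, the ceiling with 20 in the intervention arm would be 20/200 = 10 %.

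**The case against.** Agreeing over eligible is what the recruitment section itself names as the recruitment rate, so Table 2's definition is not the wrong group on its face. This stands. The difficulty is that the planned 40 uses a different base, and that the eligible group cannot be counted by any step described for non-repliers.

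The uptake per invitation is recoverable: eligibility rate × participation rate = agreeing / invited, however eligible is counted (at 100 classed eligible, 0.50 × 0.40 = 0.20). Table 1's target of 40 is a further check that low uptake would miss. Both points stand and limit the harm. But the bar of more than 20 % is attached to acceptance, not to that product, and non-response would then show up as ineligibility.

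Table 2 is the outcome-definition table and already restricts adherence to the intervention arm. Table 4's phrase is a parenthesis in a measurement-scale column and could mean those eligible for the intervention. On that reading the tables agree and the ceiling is 100 %. This is fair, but the text does not say so, and Table 1 refers only to participants.

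A reader might infer that acceptance is bound to be inflated toward 100 %, or that adherence can never reach 90 %. The article supports neither. The first is the extreme of a 20 % to 100 % range, and nothing says that non-repliers are dropped from the eligible count. The second holds only if Table 4 overrides Table 2 and is read as covering both arms or a wider group.

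**Conclusion.** The point holds as an internal conflict over two primary feasibility rates.

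- **Adherence:** this is the firmer part, because two stated definitions differ. Counting both arms caps the rate at about 50 % (48.9 % to 51.1 % with 45 randomized) against a bar of more than 90 %. On Table 2's base the bar is attainable. The size rests on 1:1 allocation and on controls having no access to the training.
- **Acceptance:** the plan uses 20 % per invitee and reports per eligible chiropractor. With 40 of 200 agreeing, the reported figure lies between 20 % and 100 %, and the article does not say where. The size rests on an assumption about how non-repliers are classed.
- **Patient retention:** the reference to randomized patients is a wording slip with no numerical effect. The countable group is patients enrolled under randomized chiropractors.

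**What to change.** 1. In Table 4, set the adherence denominator to chiropractors randomized to the intervention arm, as in Table 2, and name that arm in Table 1's criterion.
2. Judge the acceptance criterion of more than 20 % on agreeing / invited from the random sample, counting every wave mailed. Report the eligibility rate and agreeing / known-eligible beside it, and state how invitees who do not reply are classed.
3. In Table 2's retention row, replace patients randomized with patients enrolled.

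These are changes of definition and call for no new patient data; the number invited in each wave must be reported. The cost is a less favourable acceptance figure, which may fall below the bar if a second wave was mailed.

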### Specific objectives

The specific objectives target two groups of participants: chiropractors and patients. For each group, both feasibility and efficacy potential will be estimated.For chiropractors, the feasibility objectives are to estimate the proportion who Are eligible to participate and are willing to be randomized; Comply to all study procedures, including completing the KT intervention component and implementing the CPG recommendations; and Complete the 3-month follow-up evaluation.
For patients, the feasibility objectives are to estimate the proportion who Are eligible to participate and are willing to be randomized; Adhere to all study procedures; and Complete the 3-month follow-up visit and all questionnaires.
For chiropractors, the efficacy potential objectives are to estimate The extent to which knowledge and self-efficacy changes after engaging in the KT intervention and CPG and The extent to which knowledge and self-efficacy changes after engaging in CPG.
For patients, the efficacy potential objective is To estimate the effect of their chiropractor’s KT intervention and CPG implementation changes in pain, disability, and satisfaction with care at the initial phase, as well as after 3 months of follow-up.
Other secondary objectives are to identify and provide solutions to Chiropractors’ concerns about the quality of the webinars; Potential impediments to successful initiation of the main study protocol after randomization; and Challenges that participating clinicians have with managing the study (e.g. with implementing the multimodal care and/or completing initial and follow-up questionnaires).

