For the efficacy potential analysis, we will estimate the proportion of chiropractors who endorsed a higher knowledge level post-intervention in the control group and use this as the basis for calculating the probability of achieving a response more extreme than this in the intervention group using the normal approximation to the binomial distribution (stattrek.com). For example, if 2 of 15 participants in the control group endorse a higher knowledge level, this yields an expected “success” proportion of 0.13. Based on this expected proportion or probability, if 5 or more of the 16 chiropractors in the intervention group endorsed a higher knowledge response, the probability of this occurring by chance would be 0.047. This approach will be used for each of the single indicator variables under study here (i.e. knowledge and self-efficacy).

We will use generalized estimating equations (GEEs) to adjust for anticipated correlation in measurements of observations within practices (clusters). For pain and disability, GEE will be used separately for each of these outcomes and to examine for any effect of our complex intervention over time (the follow-up period). This method extends the standard regression analysis to account for any covariance between repeated measurements of pain and disability (as separate outcomes) over time, in addition to accounting for anticipated correlation of observations within practices.

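### The only chiropractor knowledge item shown measures self-reported guideline adherence, and the timing and success rule for a higher knowledge level are not settled

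*Protocol article*

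**What the plan says.** All references are to the protocol article.

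- **Item.** Measures describes a short chiropractor questionnaire with items on knowledge and on self-efficacy. The knowledge example, introduced by e.g., is "I am following the recommendations regarding the use of clinical practice guidelines and multimodal approach for neck pain".
- **Construct and timing in the text.** The same sentence begins "Expected adherence to multimodal care by chiropractors will be measured at the end of the study using a short self-administered questionnaire".
- **Timing in the table.** Table 2 has a row labelled as adherence perception, covering knowledge and self-efficacy, with baseline and 3 months as time points. Its chiropractor retention row, which counts completion of the knowledge and self-efficacy questionnaires, gives the same two time points.
- **Objective.** Specific objectives asks for an estimate of "The extent to which knowledge and self-efficacy changes after engaging in the KT intervention and CPG", and for the same change after the guideline alone.
- **Scale.** Table 4 lists level of knowledge and self-efficacy on a "5-point Likert scale (from 1 = strongly agree to 5 = strongly disagree), ordinal".
- **Analysis.** Under Statistical analysis, "we will estimate the proportion of chiropractors who endorsed a higher knowledge level post-intervention in the control group". That proportion becomes the reference probability for the intervention arm, and the method is to be applied to knowledge and to self-efficacy.

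**The concern.** An item that asks whether someone follows a guideline captures practice as the respondent sees it. A chiropractor who knows the recommendations well but does not apply them would disagree with it. One who wrongly believes that usual practice already complies would agree. Neither answer tells us about knowledge.

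The distinction matters because the protocol's own theory depends on it. Development of the KT intervention defines the behaviour to be changed as adherence to recommended care and lists knowledge as one of nine domains that may influence that adherence. If the item is analysed as knowledge, the behaviour is reported as one of its own determinants. The main trial's designers could then conclude that the webinars work by raising knowledge when the pilot has shown only that trained clinicians rate their own compliance more favourably. Such a rating is open to bias: under Blinding, chiropractors know which intervention they receive, although they are not explicitly told their group and are kept blind to the hypotheses.

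The timing and the success rule add to this. Until it is settled whether a baseline is taken and what counts as higher, two analysts could classify the same chiropractor differently.

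**Working it through.** **1. The plan's own figure.** The only number attached to this endpoint is the worked example under Statistical analysis: 2 of 15 control chiropractors succeed, 5 or more of 16 succeed in the intervention arm, and the chance probability is given as 0.047.

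- Control proportion: 2/15 = 0.133, which the protocol rounds to 0.13.
- Exact binomial upper tail: P(X ≥ 5) for X ~ Bin(16, 0.13) = 1 − Σ(k = 0 to 4) C(16, k) × 0.13^k × 0.87^(16−k) = 0.0471. This reproduces 0.047.
- Normal approximation, the method named in the text: mean 16 × 0.13 = 2.08; SD √(16 × 0.13 × 0.87) = 1.345. With continuity correction, z = (4.5 − 2.08)/1.345 = 1.80, giving 0.036. Without it, z = (5 − 2.08)/1.345 = 2.17, giving 0.015.

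So the figure is an exact binomial result, not the approximation named. That is a separate matter. For this point, what counts is that the calculation takes the number of successes as given. Item wording, timing and direction decide who is counted as a success before any probability is computed, so the arithmetic can neither reveal nor correct a fault in them.

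**2. Construct.** The labels attached to these items differ from place to place:

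| Place | What it is called |
|---|---|
| Development of the KT intervention | Adherence is the target behaviour; knowledge is one of nine influences on it |
| Measures, text | Expected adherence, with items about knowledge |
| Measures, Table 2 | Adherence perception, with knowledge and self-efficacy in brackets |
| Statistical analysis, Table 4 | Level of knowledge |
| Statistical analysis, efficacy potential | A higher knowledge level |

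The wording of the quoted item fits the Measures and Table 2 labels. It does not fit the labels under which results will be analysed.

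**3. Timing.** The Measures text mentions the end of the study. Two rows of Table 2 give baseline and 3 months, and Specific objectives requires change, which needs a baseline. Table 4 describes the efficacy comparison as post-intervention between groups. The balance favours a baseline, but the text and the table do not agree.

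**4. Reference and direction.** The analysis names no reference for *higher*. Two readings are open, and they can disagree. As an illustration on Table 4's coding, with agreement at 3 months taken as a score of 2 or less:

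| Baseline → 3 months | More agreement than own baseline | Agreement at 3 months |
|---|---|---|
| 4 → 3 | success | not success |
| 2 → 2 | not success | success |
| 4 → 2 | success | success |

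On direction, all three items quoted in Measures (one knowledge, two self-efficacy) are worded so that agreement is the favourable answer, and agreement is the low end of the scale. A move from 4 to 2 is an improvement, with a score change of 2 − 4 = −2. A move from 2 to 4 is a deterioration, with a change of 4 − 2 = +2. If higher were read as a higher number, both would be misclassified; if read as more agreement, both would be right. The protocol does not say which. The general rule under Statistical analysis, to classify response by a published or recommended MCID, does not settle it, because the article states none for these items.

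**The case against.** The strongest reply has four parts.

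- **One example.** The item is introduced by e.g., the text speaks of items in the plural and cites sources, and the full questionnaire is not shown. This stands. The point covers the item shown and any other knowledge item worded as practice; it does not show that every knowledge item has the fault.
- **Direction.** A reader might infer that the plan counts deterioration as success. The documents do not support that. The analysis speaks of endorsing a higher knowledge level or response, never of a higher score, and to endorse a statement ordinarily means to agree with it. Table 4 gives anchors, not a success rule, and recoding is often left to an analysis plan. What remains is an ambiguity that one sentence would remove.
- **Timing.** A reader might infer that the questionnaire is given only at the end, so that no change can be computed. The word *only* does not appear, and Table 2 and the objective point to a baseline. What remains is a contradiction to reconcile. Nor is a baseline answer meaningless: Context and purpose of the study says the guideline had already been updated, and the chiropractor exclusion criteria report that over 700 chiropractors had already registered for the related webinars and module.
- **Importance.** Knowledge and self-efficacy are secondary outcomes in a pilot whose main analysis is descriptive. The Abstract also describes a separate checklist of guideline compliance in the encounter forms at study onset and 3 months. This stands and limits the consequence. It does not remove it, because the binomial calculation for chiropractors is specified for knowledge and self-efficacy alone.

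**Conclusion.** The point holds for the item shown. It measures self-reported adherence to the guideline, which the protocol's own framework treats as the target behaviour, and the analysis would report it as knowledge. Alongside this, the Measures text and Table 2 disagree on when the questionnaire is given, and the success rule fixes neither the reference nor the direction of higher.

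It would go too far to say that higher knowledge cannot be read from the questionnaire at all: the remaining items are not shown, Table 2 provides for a baseline, and score reversal is a risk of the ambiguity, not a stated rule.

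The size is one of interpretation and cannot be put as a number. Recruitment, retention and intervention-completion rates are untouched, and the 0.047 example does not depend on it. What is affected is whether the pilot can say anything about knowledge as a step between the KT package and practice. The conclusion assumes that the quoted item is typical enough of the questionnaire to have been chosen as its example. It should be corrected before the chiropractor questionnaires are analysed.

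**What to change.** 1. **Relabel.** Report the quoted item, and any other knowledge item worded as practice, as self-reported guideline adherence, and draw no conclusion about knowledge from it. This costs nothing beyond the edit.
2. **Measure knowledge only if it is to be claimed.** Add a few factual items drawn from the guideline's recommendations, not copied from the webinar quizzes, and given identically to both arms. Trial status reports 45 chiropractors already randomized, so new items have no clean pre-randomization baseline; compare them between arms at 3 months. The cost is a few extra minutes per chiropractor.
3. **Timing.** Change the Measures text to baseline and 3 months, in line with Table 2 and the objective of estimating change. If the baseline questionnaire was not in fact given, say so and restrict the analysis to a 3-month comparison between arms.
4. **Success rule.** State under Statistical analysis that success is movement toward agreement from the chiropractor's own baseline, or reverse-code the items so that a higher number is the better answer and define success as an increase. This is one sentence and a coding rule.
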